#### Assessment protocol

Each of the six assessment timepoints will include a combination of semi-structured interviews completed via video call (including LS/CMI at all timepoints, C-SSRS at baseline and final follow-up, and QuickSCID and SID-P-IV at baseline) and self-report questionnaires self-administered via Qualtrics. See Table 4. To minimize bias in assessment, all interviews will be completed by evaluators who are blind to participant condition. Veterans will receive monetary compensation ($75) for each completed assessment; a completion bonus ($75) will also be provided at the end of study participation to participants who complete all assessment timepoints to encourage retention throughout the follow-up period. A random 20% of interviews will be recorded and reviewed by a second rater to assess fidelity to assessment administration protocols and determine inter-rater reliability.

**Table 4 Tab4:** Projected assessment schedule

Assessment	Construct	Baseline	8 weeks	16 weeks	28 weeks	40 weeks	52 weeks
Participant Characteristics							
Demographic Assessment	Demographic background	X					X
Chart & Records Review	Psychiatric treatment history, Military service history, Suicide-related behavior history, History of criminal-legal involvement						X*
QuickSCID / SID-P-IV	Mental health diagnoses	X					
C-SSRS	Suicide-related behavior history	X					X*
Primary Outcomes							
LS/CMI	Risk for criminal behavior, History of criminal-legal involvement	X	X	X	X	X	X
IPF	Psychosocial functioning	X	X	X	X	X	X
Secondary Outcomes							
BSS	Risk for suicide-related behavior	X	X	X	X	X	X
SNSI	Non-suicidal self-injury	X		X			X
DERS-18	Emotion regulation difficulties	X	X	X	X	X	X
TriPM	Psychopathic personality traits	X		X			X
MOCTS	Criminogenic thinking style	X		X			X
PHQ-9	Psychological distress	X	X	X	X	X	X
AUDIT	Alcohol use	X	X	X	X	X	X
DAST-10	Non-alcohol substance use	X	X	X	X	X	X
DBT-J CM Checklist	Case management needs	X	X	X	X	X	X
Q-LES-Q-SF	Quality of life	X	X	X	X	X	X
CD-RISC	Resilience	X	X	X	X	X	X
PCL-5	PTSD symptom severity	X		X			X

^*^Or at time of study termination

A data safety monitoring board (DSMB) comprised of research psychologists with experience in high-risk Veteran populations and intervention development research will aid in monitoring ongoing data collection to evaluate for potentially adverse effects of study participation. Collected data will be shared with the DSMB at least quarterly or within 48 h of an adverse event, whichever occurs first.

### Data analysis plan

Analyses will employ an alpha of 0.05, use two-tailed tests, and be completed using SPSS and/or the R Computing Environment. Preliminary analyses will include computing descriptive statistics and inspecting data to determine whether data transformations are needed, statistical assumptions are met, and psychometric properties of each scale are sound. Multiple imputation will be used for transient missing data. Because participants who dropout of the protocol may be qualitatively distinct from protocol completers (e.g., due to differences in motivation, legal requirements, etc.), analyses will also include a sensitivity analysis by comparing the full “intent-to-treat” sample against protocol completers. Potential confounders, including duration of outside treatment services received during the intervention period, will be compared across conditions and included as covariates in subsequent analyses if significantly related to study outcomes.

Primary and secondary analyses will be investigated using analyses of covariance to compare participants in the DBT-J and supportive group conditions on primary and secondary continuous treatment targets at post-treatment after controlling for baseline scores. Poisson regression with robust error variance will similarly be used to compare DBT-J and comparison conditions on dichotomous secondary treatment targets (suicide attempt during study period and criminal recidivism during study period). The DBT-J condition will be considered superior to the supportive group condition if participants in the DBT-J condition demonstrate statistically superior scores on either primary treatment target at post-treatment. The DBT-J intervention will be considered efficacious if results suggest (a) superiority to the supportive group condition and (b) clinically significant change in primary efficacy outcomes from baseline to post-treatment among DBT-J participants [67].

To support exploratory analyses comparing efficacy of DBT-J programming across VCLI subgroups, DBT-J participants will be coded according to most recent offense type (violent or nonviolent), presence of a substance use disorder, and presence of a severe mental illness (i.e., mood or psychotic disorder). Multivariate analyses of covariance will be used with subgroup membership included as predictor variables, LS/CMI and IPF post-treatment scores included as dependent variables, and LS/CMI and IPF baseline scores included as covariates.

Lastly, exploratory analyses will examine potential long-term consequences of participation in DBT-J versus supportive group therapy on primary efficacy outcomes. Two repeated-measures analyses of variance will be used with condition included as the independent variable and LS/CMI or IPF total scores at each assessment timepoint included as dependent variables.

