#### Primary efficacy outcomes

To inform primary aim analyses, participants will complete measures of risk for criminal behavior and psychosocial functioning at all assessment timepoints. Risk for criminal behavior will be assessed using the LS/CMI, described above. Psychosocial functioning will be assessed using the Inventory of Psychosocial Functioning (IPF; [32], an 80-item, self-report instrument measuring functional impairments in romantic relationships, family relationships, work, friendships and socializing, parenting, education, and self-care. Scores are interpreted through comparison to normative data of Veterans [55]. Previous research suggests the IPF to have strong construct validity, concurrent validity, internal reliability, and test–retest reliability [55].

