#### Justification of sample size

A priori power analysis was used to determine an appropriate sample size to support primary aim analyses. Informed by results of previously collected pilot data [20, 35], we anticipated at least a moderately-sized difference across conditions in primary efficacy outcomes at post-treatment. Power analysis results suggested at least 80 participants per condition (160 total) are needed to achieve 80% power to reject the null hypothesis of equal means when the population mean difference is *d* = 0.50 and α = 0.025 (to adjust for multiple comparisons). After adjusting for an anticipated dropout rate of 20%, 100 participants per condition (200 total) are required to achieve necessary statistical power.

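### The 0.025 level used to size the trial for two primary outcomes is not carried into the either-outcome superiority rule, which as written runs at 0.05

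*Protocol article*

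**What the plan says.** The protocol article fixes four things that bear on this point.

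- **Level and sidedness** (Data analysis plan): "Analyses will employ an alpha of 0.05, use two-tailed tests". No separate level, split, hierarchy or adjustment is given for the primary outcomes.
- **Primary outcomes** (Primary efficacy outcomes): there are two. The LS/CMI measures risk for criminal behaviour and the IPF measures psychosocial functioning. Each is compared between arms after treatment by ANCOVA with baseline adjustment.
- **Decision rule** (Data analysis plan): DBT-J counts as superior "if participants in the DBT-J condition demonstrate statistically superior scores on either primary treatment target at post-treatment". One significant outcome is enough.
- **Level used for planning** (Justification of sample size): "α = 0.025 (to adjust for multiple comparisons", with d = 0.50 and 80% power. This gives 80 evaluable per arm, and 100 per arm enrolled after 20% dropout.

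A further label, efficacious, needs superiority and also "clinically significant change in primary efficacy outcomes from baseline to post-treatment among DBT-J participants".

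**The concern.** A rule that accepts a win on either of two outcomes gives chance two opportunities. The sample size paragraph recognises this and pays for it by halving alpha. The analysis section, which governs how the result is declared, names only 0.05.

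The two sections can return different answers on the same data. Suppose the smaller of the two primary p-values is 0.04 and favours DBT-J. Under the Data analysis plan the trial declares superiority. At the level used to size the trial it does not. The trial's main between-arm conclusion would then depend on which paragraph is followed, and nothing in the article settles that in advance. If the analysis section is followed, the error rate is about twice the planned one, and the stated 80% power belongs to a different test from the one carried out.

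**Working it through.** **Inputs.** From the article: d = 0.50, power 80%, 80 evaluable per arm, dropout 20%, alpha 0.025 (sample size) and 0.05 two-tailed (analysis), two primary outcomes, either-outcome rule. Not in the article: the correlation r between the two outcomes. It is assumed here to lie between 0 and 0.9, and results are shown across that range.

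**Step 1: reproduce the planned sample size.** The normal approximation per arm is n = 2(z₁₋α/₂ + z₀.₈₀)² / d².

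- Two-sided 0.025: 2 × (2.241 + 0.842)² / 0.25 ≈ 76.0, rounded up to 77. The two-sample t-test gives 77.3, rounded up to 78.
- Two-sided 0.05 (the same as one-sided 0.025): 2 × (1.960 + 0.842)² / 0.25 ≈ 62.8, rounded up to 63. The t-test gives 63.8, rounded up to 64.
- One-sided 0.05: 50 by the normal approximation, 51 by the t-test.

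Only two-sided 0.025 comes within two of the stated 80. Dropout: 80 / (1 − 0.20) = 100 per arm, as stated. The 0.025 is therefore a real split of a two-sided 0.05 across two outcomes, and not a one-sided restatement of the analysis section's level.

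**Step 2: error of the either-outcome rule when neither outcome has a true effect.** Let c = 1.960 at 0.05 and c = 2.241 at 0.025, and let Z₁ and Z₂ be bivariate normal with correlation r.

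- False claim favouring DBT-J: 1 − P(Z₁ < c, Z₂ < c). At r = 0 this is 1 − 0.975² = 4.94% at 0.05 each, and 1 − 0.9875² = 2.48% at 0.025 each.
- Two-sided family-wise error: 1 − P(|Z₁| < c, |Z₂| < c). At r = 0 this is 1 − 0.95² = 9.75% at 0.05 each, and 1 − 0.975² = 4.94% at 0.025 each.

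| r (assumed) | False DBT-J claim, 0.05 each | False DBT-J claim, 0.025 each | Two-sided, 0.05 each | Two-sided, 0.025 each |
|---|---|---|---|---|
| 0 | 4.94% | 2.48% | 9.75% | 4.94% |
| 0.3 | 4.76% | 2.42% | 9.51% | 4.84% |
| 0.5 | 4.54% | 2.32% | 9.07% | 4.65% |
| 0.7 | 4.17% | 2.15% | 8.35% | 4.30% |
| 0.9 | 3.52% | 1.81% | 7.04% | 3.62% |

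For reference, a single two-sided 0.05 test has a 2.5% chance of a false result in favour of DBT-J.

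**Step 3: power at the planned size.** By two-sample t-test with 80 per arm and d = 0.50, power per outcome is 81.5% at two-sided 0.025 and 88.2% at two-sided 0.05.

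**The case against.** The strongest reply is that the two sections can be read together. The 0.05 may be the overall level, and 0.025 is 0.05/2, given with multiplicity as its reason. On that view the sponsor always meant to test each primary outcome at 0.025, and an analysis plan that is not shown may say so. Part of this stands: the sample size shows that a split was intended, and it is not established that the trial will in fact test each outcome at 0.05. But the article does not call 0.05 a family-wise level, and it attaches the either-outcome rule to that level without qualification. The finding is this mismatch between two stated levels, not missing procedural detail. An unseen document could settle which level applies, but it could not make both statements correct as the rule for the primary tests.

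Three stronger readings are tempting, and the article does not support them.

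- *That the risk of a wrong headline is 9–10%.* That figure counts significant results in either direction, and a result favouring supportive therapy cannot trigger the superiority claim. Even as a two-sided figure it holds only for correlations up to about 0.5. It falls to 7.0% at 0.9, and the article gives no correlation.
- *That an either-outcome rule is wrong in itself because one win may stand while the other outcome is worse.* Such a rule is legitimate once alpha is split. Whether to restrict the claim to the outcome that passed is a separate preference.
- *That the trial is underpowered.* It is not: the planned number suffices at either level.

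A reader might also expect the second condition, for the efficacious label, to protect the claim. It does not. It is assessed within the DBT-J arm without a control, and the superiority claim does not require it.

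**Conclusion.** The point holds as an internal contradiction with a measurable consequence. The analysis section's level and rule, followed literally, roughly double the planned error. The probability of a false DBT-J superiority claim is about 3.5–4.9% against 1.8–2.5% under the split, and the two-sided family-wise error is about 7–9.75% against 3.6–4.9%. These figures assume no true effect on either outcome, approximately normal test statistics, and a correlation from 0.9 (lower end) to 0 (upper end). The doubling itself depends little on the correlation; the absolute values do. Because the rule decides the trial's main between-arm conclusion, it should be settled before outcomes are examined by arm.

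**What to change.** In the Data analysis plan, add wording to this effect: LS/CMI and IPF at post-treatment are each tested at two-sided 0.025 (or by Holm at family-wise 0.05: the smaller p-value against 0.025 and, if it passes, the other against 0.05), and statistically superior in the either-outcome rule means significant at that level. The either-outcome claim comes out the same under both options, since each first compares the smaller p-value with 0.025. Holm only makes it easier to claim the second outcome as well.

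The cost is a sentence or two, with a check that any analysis plan or registration entry not shown here agrees. The planned 80 evaluable and 100 enrolled per arm stay as they are, because they were calculated at 0.025 and give 81.5% power per outcome at that level.

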### Participants

Veterans will be recruited via referral from local mental health providers, VA VJP Specialists, treatment court providers, and local Veteran service organizations and via self-referral through mail-based recruitment. To be considered for inclusion, Veterans must be aged 18 + ; able to provide consent (i.e., have capacity to understand the study’s purpose, risk, and benefits and make an informed decision about participation); and have a recent history of criminal-legal involvement, defined as criminal arrest, order of protection, or incarceration within two years prior to participation and/or supervision by probation or parole at the time of enrollment. Exclusion criteria include limited English proficiency; inability to tolerate group therapy format; concurrent enrollment in another clinical trial; concurrent enrollment in interventions based in the RNR model (e.g., MRT) or DBT; and prior participation in DBT-J. Using similar inclusion/exclusion criteria, prior studies have yielded VCLI samples that are predominantly male with notable heterogeneity in race, ethnicity, age, presenting mental health concerns, and criminal-legal history [20, 35]. To maximize generalizability of results to the heterogeneous population of VCLIs, no inclusion/exclusion criteria related to psychopathology and/or VA eligibility will be used. VCLI experience a range of psychosocial needs [7], and many are not eligible for comprehensive VA care due to discharge status or other barriers [46]. Previous trials have successfully enrolled VCLIs across the psychosocial need spectrum, including those with active suicidal ideation, homelessness, psychotic disorders, and severe substance use [20, 35], suggesting feasibility of this flexibility in inclusion/exclusion criteria.

Consistent with previous DBT-J trials [20, 35], we anticipate a dropout rate of 20% during the intervention period, resulting in a final sample size of approximately 160 at post-treatment. Participants are considered to have dropped out of participation after missing four consecutive group sessions. There are otherwise no attendance requirements for participation.

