### Anticipated limitations

Due to under-representation of women in VCLI samples [68], we anticipate difficulties obtaining a sample that will support analyses surrounding potential sex differences. To offset this potential limitation, recruitment efforts will attempt to over-sample for women through specific outreach to VA providers specializing in the care of female Veterans. Further, although previous research suggests low attrition rates from DBT-J, ample research attests to the tendency for Veterans to dropout of standard behavioral health services prematurely [69]. It is therefore possible that attrition will be higher than expected during the intervention period, particularly for VCLIs assigned to the comparison condition. The study design also does not allow for explicit comparisons of DBT-J against current standard of care for VCLIs. Should results suggest DBT-J to be an efficacious treatment, continued research should explore this comparison.

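### Multiple imputation is limited to transient gaps, so the promised full intent-to-treat analysis at week 16 has no stated way to include the roughly 40 participants expected to drop out

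*Protocol article*

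**What the plan says.** Four statements in the protocol article bear on this.

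- **Missing data.** The Data analysis plan states: "Multiple imputation will be used for transient missing data". Its next sentence takes dropouts as a separate group. It begins "Because participants who dropout of the protocol may be qualitatively distinct from protocol completers" and concludes that "analyses will also include a sensitivity analysis by comparing the full “intent-to-treat” sample against protocol completers".
- **Primary model.** The same section compares the arms by analysis of covariance on "primary and secondary continuous treatment targets at post-treatment after controlling for baseline scores". Post-treatment is week 16.
- **Dropout.** Under Participants: "Participants are considered to have dropped out of participation after missing four consecutive group sessions". The same paragraph says "we anticipate a dropout rate of 20% during the intervention period, resulting in a final sample size of approximately 160 at post-treatment". The Justification of sample size powers the trial on those 160 and inflates to 200.
- **Attrition by arm.** Anticipated limitations names as a possibility that "attrition will be higher than expected during the intervention period, particularly for VCLIs assigned to the comparison condition".

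The article does not say whether outcome assessments stop or continue after dropout, or whether the intent-to-treat or the completer analysis is primary.

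**The concern.** Dropout is defined by therapy attendance but counted as loss from the outcome data. An ANCOVA at week 16 can use only participants who have a week-16 score, observed or imputed. Imputation is reserved for transient gaps, and leaving for good is not a transient gap. Followed as written, the plan promises a full intent-to-treat set and gives no route by which dropouts enter it.

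At stake is the primary comparison on both primary outcomes, the LS/CMI and the IPF. If dropouts are absent at week 16, the analysis called intent-to-treat is in practice close to a completer analysis. Setting it beside the completers then compares almost the same people twice. The article itself gives the reason to worry: dropouts may be a different kind of participant, and the two arms may lose different numbers of them.

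**Working it through.** **1. The plan's own figures.** Inputs from Justification of sample size: d = 0.50, α = 0.025 (taken as two-sided), power 80%, dropout 20%.
- Required per arm: 78 by the noncentral t, 77 by the normal approximation. At the stated 80 per arm, power is 0.815. The stated figure is reproduced and slightly conservative.
- Inflation: 80 / (1 − 0.20) = 100 per arm, 200 in total.
- Planned without week-16 data: 200 − 160 = 40.

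The 80% power therefore rests on about 160 people with week-16 scores, and the same 20% loss is applied to both arms.

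**2. The two readings side by side.**
- *Dropouts are not assessed at week 16.* This fits the 160 and the word transient. The full intent-to-treat set then has no values for about 40 people, nearly coincides with the completers, and the sensitivity comparison shows little.
- *All 200 are analysed.* This fits the intent-to-treat label. The 160 at post-treatment and the transient limit then conflict with it, and the power basis changes. If completers differ by 0.50 and dropouts show no difference between arms (an assumption), the effect over all randomised is 0.80 × 0.50 + 0.20 × 0 = 0.40. With 100 per arm at α = 0.025, power is then 0.715.

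Either way, the passages need to be reconciled.

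**3. Size of possible bias under the first reading.** Orient scores so that higher is better. Let p be the dropout share in an arm, C its completer mean, and g the amount in SD by which dropouts would score worse than completers, equal in both arms.
- Mean of all randomised in an arm = (1 − p)C + p(C − g) = C − p·g.
- Completer contrast minus all-randomised contrast (DBT-J minus comparison) = (p_DBT-J − p_comparison) × g.

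The article gives neither arm-specific rates nor g, so both are assumed:

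| Dropout DBT-J / comparison | g = 0.25 | g = 0.5 | g = 1.0 |
|---|---|---|---|
| 20% / 20% | 0 | 0 | 0 |
| 15% / 25% | −0.025 | −0.05 | −0.10 |
| 10% / 30% | −0.05 | −0.10 | −0.20 |

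A minus sign means the completer contrast understates DBT-J. If dropouts do better than completers, or leave more often from the DBT-J arm, the sign turns. The largest entry is 0.20 / 0.50 = 40% of the planned effect. If the gap differs by arm, the bias is p_DBT-J × g_DBT-J − p_comparison × g_comparison, so equal rates alone do not guarantee zero.

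**4. Power is not the main issue.** With 160 completers in total, an unequal split costs little at d = 0.50: 0.813 at 85/75 and 0.808 at 90/70, against 0.815 at 80/80. The issue is who is missing.

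**The case against.** The strongest reply is that the article nowhere says assessments end when someone drops out of therapy. They are separate from the groups: interviews by video call, questionnaires online, paid per assessment, with a bonus for completing all. DBT-J engagement strategies ties the fourth consecutive absence only to the option of returning to the programme. The authors distinguish a full intent-to-treat sample from completers, so they mean to analyse both, and the 160 may be no more than a cautious power assumption. If dropouts are in fact assessed at week 16, the two sets differ and the sensitivity analysis is informative.

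This stands in part. That dropouts lack week-16 scores is an inference. It is a strong one, because the article itself calls about 160 the final sample at post-treatment, and a note to Table 4 moves the final C-SSRS and records review to study termination, which foresees early exit.

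Four stronger readings are tempting, and the document does not support them:
- *Higher dropout is expected in the comparison arm.* Anticipated limitations calls it only possible, and planning uses 20% in both arms.
- *The week-8 scores are ignored.* The ANCOVA does not use them, but the imputation model is not described and could.
- *The primary result is biased by up to 0.20 SD.* That needs assumed rates and gaps, and the calculation uses raw means. The ANCOVA adjusts for baseline, so only the part of the gap that baseline does not explain would remain.
- *The plan is deficient for omitting an imputation model or a missing-not-at-random analysis.* An article commonly leaves these to the analysis plan. The point here is narrower: a stated limit on imputation conflicts with a stated analysis set.

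**Conclusion.** The point holds as an internal conflict. Imputation is confined to transient gaps, about 40 of 200 are counted out at post-treatment, and a full intent-to-treat comparison at week 16 is promised with no stated method for including them. If dropouts are not assessed at week 16, the only planned sensitivity analysis cannot show selective dropout.

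The size is illustrative: zero under the plan's own equal 20% with equal gaps, and up to 0.10 or 0.20 SD at the assumed 15%/25% and 10%/30% with a gap of 1 SD, before baseline adjustment. The direction is unknown. Because both primary outcomes depend on it and uncollected scores cannot be recovered, it should be settled while assessments are still running.

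**What to change.** 1. Reconcile Participants with the Data analysis plan. State that missing group sessions does not end outcome assessment, and that the scheduled remote assessments, week 16 above all, are sought from everyone who has not withdrawn consent. This concerns data collection only and leaves the attendance rule for therapy as it is.
2. Name the analysis of all randomised participants as primary. Delete the transient limit, so that multiple imputation by arm, using baseline and week-8 scores, covers dropouts. A likelihood-based mixed model would serve equally well; ANCOVA need not be abandoned.
3. Keep the completer comparison as supplementary, and add a delta-adjusted missing-not-at-random sensitivity analysis.

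Cost: a little more analysis work, plus payments and blinded interviewer time for up to about 40 participants. At $75 per assessment, week 16 alone is 40 × $75 = $3,000. All five post-baseline assessments would be at most 40 × 5 × $75 = $15,000, plus up to 40 × $75 = $3,000 in completion bonuses. These are upper bounds, and they are new money only if such assessments are not already budgeted. Recruitment has been planned since 2024, so assessments already missed by earlier dropouts cannot be recovered and must be handled by imputation.
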